### Safety

An independent Data Safety Monitoring Committee (DSMC) has been appointed to assess protocol adherence, patient recruitment, and patient safety. All physicians who are involved in the trial are asked to report all adverse events to the coordinating investigator. Adverse events are reported using the online module (https://www.toetsingonline.nl) of the Dutch Central Committee on Research involving human subjects. All adverse events are collected and reported unblinded to the DSMC every time 60 patients are randomized, after randomization of the final patient, and at the end of follow-up of the final patient. In addition, a continuous sequential safety analysis on mortality is performed to ensure the patient’s safety throughout the trial. The DSMC discusses all adverse events and the progress of the trial and reports to the trial steering committee. A copy is sent to the ethical committee and all physicians who are involved with the study.

### Ethics

The APEC trial is performed in accordance with the declaration of Helsinki and the Dutch law regarding research involving human subjects (Wet Medisch wetenschappelijk Onderzoek met Mensen). Informed consent will be obtained from each participant. The ethical committee of the Erasmus Medical Center in Rotterdam, the Netherlands, approved the study protocol on the 12th of December 2012. Subsequently, the boards of the 27 participating hospitals gave permission for conducting the trial (see Additional file 8 Ethical bodies that approved the trial). The APEC trial is registered with identification number ISRCTN97372133.

### Statistical considerations

#### Sample size calculation

The sample size calculation is based on a recent Dutch multicenter observational study of patients with biliary pancreatitis at high risk for complications [11]. The primary endpoint occurred in 32 % of the patients in which ERC was performed compared with 46 % of the patients who were treated conservatively. Taking into account that ERC was not always performed within 24 hours and that sphincterotomy was not routinely performed, a correction factor of 2 % for both percentages is added to both incidence rates. The APEC trial is a superiority trial in which the sample size calculation is based on the assumption that early ERC with sphincterotomy reduces the incidence of the primary endpoint by 18 % (48 % to 30 %). With a power of 80 %, a two-sided significance level of 5 % and a 1 % drop-out rate, a total of 232 patients are required to be included in the study (http://www.stat.ubc.ca/~rollin/stats/ssize/b2.html, accessed 20 July 2015)).

#### Descriptive statistics

The following patient characteristics before randomization will be described: age, sex, body mass index, comorbidity, American Society of Anesthesiologists (ASA) score, duration of symptoms before randomization, duration of symptoms before ERC, serum bilirubin levels, dilated common bile duct on ultrasound or computed tomography, presence of (multi) organ failure or systemic inflammatory response syndrome (SIRS), Sequential Organ Failure Assessment (SOFA) scale [28], Multiple Organ Dysfunction Score (MODS) [29], predicted disease severity according to APACHE-II, modified Glasgow, blood urea nitrogen, and C-reactive protein. Data will be presented in percentages for categorical variables. Continuous data with a normal distribution will be presented as a mean with standard deviation and as median with interquartile range in case of skewed distribution.

#### Analyses

After 232 patients have completed their 6 months of follow-up, raw data regarding potential endpoints will be presented to an adjudication committee blinded to the treatment allocation to determine whether the endpoints meet the protocol-specified criteria. The study coordinator will blind the patient reports for treatment allocation. Each member of the committee will individually assess the potential endpoints. In case of dissenting opinions, a consensus meeting will follow. Only after consensus has been reached on each individual endpoint for each individual patient will a final analysis be performed by an independent statistician, unblinded for treatment allocation. Primary analysis, using the Pearson’s Chi-squared test, is based on the intention-to-treat principle, with patients being analyzed according to original treatment allocation, regardless of whether the cannulation or sphincterotomy was successful. For exploratory reasons a per-protocol analysis will be performed to compare treatment groups. A tabular listing of all patients excluded from the intention-to-treat populations will be provided together with the reasons for exclusion. Data will be presented as relative risks with 95 % confidence intervals. A two-tailed P < 0.05 is considered statistically significant.

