### Randomization

Patients are randomized to early ERC with sphincterotomy or to conservative treatment (1:1 ratio) with a web-based randomization module (ALEA, Academic Medical Center, Amsterdam, The Netherlands) in random blocks of two, four or six. At randomization, patients are stratified according to the presence of cholestasis and for region of the hospital. Cholestasis is defined as a serum bilirubin > 40 μmol/L at randomization or a dilated common bile duct (defined as > 8 mm in patients ≤ 75 years or > 10 mm in patients > 75 years).

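### The primary test ignores the factors that randomization is stratified by, so it is mildly conservative to the extent that cholestasis and region predict the outcome

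*Protocol article*

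**What the plan says.** In the protocol article, the Randomization section describes 1:1 allocation "in random blocks of two, four or six", and "patients are stratified according to the presence of cholestasis and for region of the hospital". The number of regions is not given.

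The Analyses section sets the primary comparison as a Pearson test: "Chi-squared test, is based on the intention-to-treat principle, with patients being analyzed according to original treatment allocation". On estimation it says: "Data will be presented as relative risks with 95 % confidence intervals". Neither sentence mentions strata or covariates.

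The stratification factors appear elsewhere as follows:
- **Cholestasis** is used in a predefined subgroup analysis with a logistic test of interaction, and as one candidate in an exploratory covariate model (Additional analyses).
- **Region** is used in no analysis that the article describes.
- **A multivariable analysis of the primary endpoint** is listed under Secondary endpoints, but it runs only if baseline variables differ significantly between the arms.

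**The concern.** Randomizing in blocks within strata forces the arms to be nearly balanced on cholestasis and region. If those factors are prognostic, the treatment difference varies less from trial to trial than it would under simple randomization. The Pearson test estimates its standard error as if the strata did not exist, so that standard error still contains the between-stratum variation. The P value is then too large on average and the confidence interval too wide.

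The conditional multivariable analysis does not repair this. Stratification makes a significant baseline difference unlikely for exactly these two factors, so the trigger would rarely fire on their account, and the result would be secondary in any case.

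What is at stake is some precision and power in a trial sized with almost no reserve above 80%.

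**Working it through.** **1. The plan's own figure.** Inputs from Sample size calculation: 48% versus 30%, two-sided 5%, 80% power, 1% drop-out, total 232. With the pooled rate (0.48 + 0.30)/2 = 0.39:

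n per arm = [1.96·√(2·0.39·0.61) + 0.8416·√(0.48·0.52 + 0.30·0.70)]² / 0.18² = 1.9225² / 0.0324 = 114.1, so 115 per arm and 230 in total.

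230 / 0.99 = 232.3, which reproduces 232 to the nearest integer. An unstratified two-proportion test with 115 per arm has 80.3% power. The trial was therefore sized for the test it names.

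**2. Analytic size of the effect.** Let R² be the share of outcome variance that lies between strata. With close balance within strata, the true type I error of the unstratified test is about 2·[1 − Φ(1.96/√(1 − R²))], and its interval is too wide by a factor of about 1/√(1 − R²).

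- R² = 0: 5.0%, no excess width.
- R² = 3.9%: 1.96/√0.961 = 2.00, giving 4.6%; width factor 1.02.
- R² = 13.6%: 1.96/√0.864 = 2.11, giving 3.5%; width factor 1.08.

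**3. Simulation.** 6,000 trials per setting, N = 230, permuted blocks of 2, 4 or 6 within cholestasis-by-region strata. Type I error was run at 39% in both arms and power at 48% versus 30%. The documents do not give cholestasis prevalence, number of regions or prognostic strength, so all three are assumptions. Region effects are normal quantiles on the log-odds scale with the SD shown. CMH is the Cochran-Mantel-Haenszel test over all strata.

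| Prevalence | Regions | Cholestasis OR | Region SD | R² | Type I: Pearson / CMH | Power: Pearson / CMH |
|---|---|---|---|---|---|---|
| 30% | 5 | 1 | 0 | 0% | 4.9% / 4.8% | 80.4% / 79.8% |
| 30% | 5 | 1.5 | 0.2 | 1.5% | 5.0% / 5.1% | 81.0% / 81.2% |
| 30% | 5 | 2 | 0.3 | 3.9% | 4.4% / 4.7% | 81.6% / 82.2% |
| 50% | 5 | 2 | 0.3 | 4.2% | 4.5% / 4.8% | 81.5% / 82.5% |
| 30% | 5 | 3 | 0.3 | 7.4% | 4.5% / 5.3% | 80.7% / 82.6% |
| 50% | 5 | 3 | 0.3 | 8.0% | 4.5% / 5.2% | 82.3% / 83.6% |
| 30% | 5 | 4 | 0.5 | 12.5% | 3.9% / 4.8% | 81.0% / 84.2% |
| 50% | 8 | 4 | 0.5 | 13.6% | 3.5% / 5.2% | 83.8% / 86.5% |

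The Monte Carlo standard error is about 0.3 points for type I error and 0.5 points for power.

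**4. Reading.** The power forgone (CMH minus Pearson) is at most about 1 point for odds ratios of 1.5 to 2, 1 to 2 points for an odds ratio of 3, and about 3 points for an odds ratio of 4 with a strong region effect. With no prognostic strata, CMH is 0.6 points lower, which is within simulation noise. Pearson power stays above 80% in every setting.

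**The case against.** The strongest reply is that nothing promised is lost. The sample size was calculated for an unstratified comparison, that comparison keeps its 80% power, and its error rate can only fall below 5%. The harm depends on the strata being prognostic, and the article reports no event rate by cholestasis or region. All of this stands, and it limits the point to an optional gain.

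Three stronger readings are tempting, and the documents support none of them.

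- **That the loss is large.** A type I error near 3.1% and a gain near 6 power points can be produced, but only with a 40-point risk gap by cholestasis plus a 30-point range across regions. Taken additively and centred, that puts the lowest-risk stratum of the ERC arm at 30 − 20 − 15 = −5%, which is impossible without truncation.
- **That the article itself shows cholestasis to be prognostic.** The Background and Discussion passages on cholestasis concern whether the benefit of ERC depends on it. That is effect modification, which the planned interaction test addresses. The nearest support for prognosis is its place among the essential covariates in Additional analyses and the Discussion's remark linking severity to duration of obstruction. Neither gives a size, and the Discussion also calls early predictors of obstruction unreliable. Nothing suggests that region is prognostic.
- **That the unadjusted relative risk is wrong for this design.** Under 1:1 stratified randomization the marginal relative risk is a valid estimate. At most its interval is somewhat wide.

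A practical objection also stands in part: with an unstated number of regions and 232 patients, some cholestasis-by-region cells may be sparse. The fix allows for that.

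**Conclusion.** The mismatch between stratified randomization and an unstratified primary analysis is in the text, and no other planned analysis removes it. The direction is certain in principle: conservative, never anti-conservative, and only to the extent that the strata are prognostic. The size is not certain. Under assumed prevalences of 30-50%, 5 to 8 regions and cholestasis odds ratios of 1.5 to 4, true type I error is about 4.4-5.0% with weak to moderate strata and 3.5-3.9% with strong ones. About 0 to 3 power points are forgone. The planned test remains valid, so this is a modest improvement that is worth making because it is almost free.

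**What to change.** Before unblinding, amend the primary analysis sentence to name one of the following:
- a Cochran-Mantel-Haenszel test stratified by cholestasis and region, with the Mantel-Haenszel relative risk and its 95% confidence interval; or
- if cholestasis-by-region cells prove sparse, a modified Poisson model with robust standard errors and main effects for treatment, cholestasis and region.

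The choice between the two should follow a rule based on cell counts pooled over arms, set before the allocation is known to the analyst. Keep the unstratified Pearson test and relative risk as a sensitivity analysis. Keep the cholestasis interaction test as planned, because a pooled relative risk summarises a common effect and the trial means to examine whether the effect is common.

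The cost is a sentence or two in the plan. Both factors are already recorded at randomization, and the sample size need not change.

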### Primary endpoint

The primary endpoint is a composite of major complications or death occurring within 180 days after randomization (that is, the composite endpoint can only occur once per patient). Major complications are defined as persistent organ failure, pancreatic necrosis, bacteremia, cholangitis, pneumonia, and pancreatic endocrine or exocrine insufficiency (see Additional file 3: Table S1 for definitions).

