### Exclusion criteria

The exclusion criteria include the following:Cholangitis (see Additional file 3: Table S1 for definition).Pancreatitis due to other causes such as alcohol abuse (more than 4 units per day), metabolic causes (hypertriglyceridemia or hypercalcemia), medication, trauma, etc.Previous pancreatic sphincterotomy or needle knife precut.Chronic pancreatitis (see Additional file 7: Table S5 for definition).International Normalized Ratio that cannot be corrected to less than 1.5 with clotting factors or fresh frozen plasma.Pregnancy.

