#### Conservative treatment

Patients in the conservative group are managed according to the conservative supportive treatment regimen for patients with acute biliary pancreatitis as described in the paragraph below. A rescue ERC is performed when a patient develops cholangitis (see Additional file 3: Table S1 for definition). Whenever the attending physician is in doubt concerning whether or not an ERC should be performed, the study coordinator presents the case to an expert panel. This expert panel, consisting of an independent gastroenterologist and a gastrointestinal surgeon, provides a treatment advice within 24 hours. Retained bile duct stones are removed during an elective ERC when the patient is recovered from the initial pancreatitis episode.

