#### Additional analyses

Predefined subgroup analysis will be done according to the presence of cholestasis. Logistic regression models will be used to test whether treatment effects differ significantly between these subgroups. Secondary endpoints will be compared using the Pearson’s chi-squared test or Mann-Whitney U test. Additionally, secondary endpoints will be analyzed separately using Cox regression analysis censoring patients no longer at risk and categorizing missing data as no event. For all other analyses, data will be considered missing at random. To evaluate differences in systemic inflammatory response after randomization, the APACHE-II, C-reactive protein levels, and presence of SIRS from randomization to day 7 will be calculated and compared between the treatment groups. To gain further insight into factors that are predictive of major complications or death after ERC, an exploratory analysis of the effects of (essential) baseline covariates (and potential interactions) will be performed using logistic regression analysis. The essential baseline covariates that will be studied are demographics, comorbidity, predicted severity prior to randomization, presence of organ failure prior to randomization, cholestasis, and duration of symptoms prior to randomization. In addition, the time between the start of symptoms and the ERC will be studied.

Direct medical and nonmedical costs and indirect costs will be compared to assess costs per patient with poor outcome (death or severe complications). Validated questionnaires will be analyzed to assess differences in the quality of life and provide input to compare costs per quality-adjusted life year (QALY). Health utility scoring algorithms for the EQ5D-5 L health status profiles available from the literature, based on preferences in the general population using time trade-off elicitation techniques, will be used to derive a QALY estimate for each patient. This QALY will be calculated as the product sum of health utilities and the lengths of the periods between the successive measurements [30, 31].

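### The as-treated analysis of the primary endpoint, if it groups by any ERC received, counts conservative patients as ERC patients because they already have an endpoint event

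*Protocol article*

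**What the plan says.** All references are to the protocol article.

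- **Secondary endpoints** lists both a per-protocol and an as-treated analysis of the primary endpoint. It gives no rule for who counts as treated and no time window.
- **Analyses** makes intention to treat primary, "with patients being analyzed according to original treatment allocation, regardless of whether the cannulation or sphincterotomy was successful". On the per-protocol analysis it says: "For exploratory reasons a per-protocol analysis will be performed to compare treatment groups". It does not mention the as-treated analysis.
- **Additional analyses** gives the test: "Secondary endpoints will be compared using the Pearson’s chi-squared test or Mann-Whitney U test". For a binary outcome this means a plain chi-squared comparison.
- **Primary endpoint**: "Major complications are defined as persistent organ failure, pancreatic necrosis, bacteremia, cholangitis, pneumonia, and pancreatic endocrine or exocrine insufficiency". Death is the other part of the composite, and each patient counts at most once.
- **Exclusion criteria** bars patients who have cholangitis at entry.
- **Conservative treatment** opens more than one route to ERC in that arm: "A rescue ERC is performed when a patient develops cholangitis"; "Retained bile duct stones are removed during an elective ERC when the patient is recovered from the initial pancreatitis episode". An expert panel can also advise on ERC in doubtful cases.
- **Early ERC with sphincterotomy** ties the experimental treatment to 72 hours from symptom onset and 24 hours from admission.

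**The concern.** Cholangitis is excluded at entry, so cholangitis that leads to a rescue ERC is a new event after randomization. It is already a primary-endpoint event when the ERC is done. If as-treated means grouping by any ERC received, each such patient leaves the conservative group and joins the ERC group with the event attached. The outcome then determines the exposure.

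The elective route adds a second distortion. Those patients have survived and recovered, so they are selected after randomization and presumably have a lower event risk. Moving them pulls the other way. Neither route reflects a baseline difference in treatment, and the net bias depends on how many patients take each route.

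The as-treated result could therefore suggest harm where there is none, or hide most of a real benefit. It could also disagree with the intention-to-treat result purely because of how patients were grouped.

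**Working it through.** **Inputs from the article.** Event rates of 48% (conservative) and 30% (early ERC), 80% power, two-sided 5%, 1% drop-out, 232 patients (Sample size calculation); 1:1 allocation (Randomization), so 116 per arm.

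**Step 1, the plan's own figures.** The planned relative risk is 0.30/0.48 = 0.625. The pooled-variance formula for two proportions without continuity correction gives 115 per arm, or 230 in total. Allowing for 1% drop-out, 230/0.99 = 232.3, which agrees with the stated 232 apart from rounding. The sample size is not in question.

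**Step 2, as-treated by any ERC received.** Let r be the share of the conservative arm that has rescue ERC for cholangitis, each with an event. The article does not give r, so 5% to 15% is an assumed range. All other patients are taken as treated as allocated. The arms are equal, so 116 cancels:

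- ERC group rate = (pE + r)/(1 + r)
- Conservative group rate = (pC − r)/(1 − r)

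| r | Planned effect (30% vs 48%) | RR | No effect (48% in both arms) | RR |
|---|---|---|---|---|
| 0 | 30.0% vs 48.0% | 0.625 | 48.0% vs 48.0% | 1.00 |
| 5% | 0.35/1.05 = 33.3% vs 0.43/0.95 = 45.3% | 0.74 | 0.53/1.05 = 50.5% vs 45.3% | 1.12 |
| 10% | 0.40/1.10 = 36.4% vs 0.38/0.90 = 42.2% | 0.86 | 0.58/1.10 = 52.7% vs 42.2% | 1.25 |
| 15% | 0.45/1.15 = 39.1% vs 0.33/0.85 = 38.8% | 1.01 | 0.63/1.15 = 54.8% vs 38.8% | 1.41 |

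At r = 10% the planned 18-point difference shrinks to about 6 points.

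**Step 3, adding elective ERC.** Assume also that 15% of the conservative arm has elective ERC with a 30% event risk, which is 0.045 of the arm as events. At r = 10% with no effect:

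- ERC group: (0.48 + 0.10 + 0.045)/1.25 = 50.0%
- Conservative group: (0.48 − 0.10 − 0.045)/0.75 = 44.7%
- RR = 1.12, compared with 1.25 in Step 2

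Under the planned effect the ERC group becomes (0.30 + 0.10 + 0.045)/1.25 = 35.6%, and 35.6/44.7 gives RR 0.80, compared with 0.86. The offset is partial in this illustration.

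**Step 4, per protocol.** Rescue and elective ERC are prescribed within conservative treatment, so these patients adhere to protocol and stay in their arm. On that account the relative risk is unchanged (0.625 or 1.00).

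**Step 5, the alternative estimator.** The complier-average estimate is the intention-to-treat risk difference divided by the between-arm difference in early ERC received. For illustration, assume 90% of the ERC arm and none of the conservative arm receive early ERC. The planned effect gives −18/0.90 = −20 points, and no effect gives 0/0.90 = 0. Later rescue and elective ERCs do not enter it.

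**The case against.** The strongest reply is that the article states no classification rule. It describes the experimental treatment throughout as early ERC in a set window, against a conservative strategy that itself includes rescue and elective ERC. Grouping on those terms leaves later ERCs in the conservative group, and the bias largely disappears. A condensed article may also leave analysis sets to the full protocol or analysis plan, which are not shown. This stands to the extent that the bias is conditional on the usual meaning of as-treated. It does not dispose of the point, because that usual meaning conflicts directly with the article's own endpoint and rescue rule.

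The Step 2 figures are also one-sided, since they leave out elective ERC and failed cannulation. This stands too: they show the rescue route alone and are not a forecast.

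A reader might infer that the per-protocol analysis has the same fault. The article does not support this, for the reason in Step 4. If rescue patients were wrongly excluded, events would be dropped from the conservative arm and none charged to ERC (at r = 10%, RR 0.71 under the planned effect and 1.14 under no effect). That is a different bias, and nothing in the article says it would be done. Nor does the article say that failed ERCs would be removed from the ERC arm.

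A reader might also infer that the trial's main conclusion is at risk, or that the as-treated result is meant as a check on it. The first is wrong, because the primary analysis follows allocation. The second is stated nowhere.

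**Conclusion.** The point holds for the as-treated analysis only, on its usual reading of any ERC received. Cholangitis is both a primary-endpoint component and the trigger for rescue ERC, so that grouping is biased against ERC through the rescue route. Selection of recovered patients through elective ERC acts in the opposite direction.

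The size rests on an assumed rescue rate. The Step 2 shifts over 5% to 15% require that every rescued patient has an event and that nobody else crosses over; elective ERC would reduce them by an amount the article does not allow one to fix. The defect is confined to one secondary analysis. Type I error, power and the conclusion of the primary analysis are untouched.

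**What to change.** In Secondary endpoints:

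1. Define treated with ERC as ERC performed within the existing early-ERC window, without conditioning on whether an endpoint event came first. Requiring the ERC to precede any event would take early events out of the ERC group and reverse the bias.
2. Keep later rescue and elective ERCs in the conservative group, as part of that strategy.
3. Label the analysis exploratory, as Analyses already does for per protocol.

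A rescue ERC that fell inside the window would still be misassigned, and any grouping by treatment received loses the protection of randomization. It is therefore preferable to replace the as-treated analysis with the complier-average estimate, using allocation as the instrument, or to report that estimate beside it. The estimate assumes that allocation affects outcome only through early ERC received, and this should be stated.

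The cost is a change of wording and one further estimate from data already collected. No more patients are needed and no clinical rule changes. The complier-average interval will be wider, and there is slightly more analysis work.
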